## The intervention

Eligible participants will be assigned randomly in to amaranth70% chilckpea30% versus maize100% 150mg daily bread groups. After randomization they will be given a card where it is stated their id-number and study participation. After assigning the participants to one of the two groups the respective 150 gm of the correct bread will be provided every day for 6 month in each group. The participants will be assigned to a ‘distributor’ who will be kept uninformed about the content of the bread he or she is distributing.

The trial will be double blinded: it means that the one receiving the amaranth70%/chilckpea30% or maize100% bread, the one distributing it and the data collectors will be kept uninformed about the trial allocation. To make the color of both bread types similar, maize will be processed (roasted) to change the color (darker). Bread distributors will be different for amaranth70% chickpes30%group and the maize100% group. Both bread distributors will get the bread from coordinator and they will distribute separately according to the trial allocation.

## Recipe, baking, packing and distribution

The recipe will be prepared based on the recommended dietary intake (RDA); according to RDA 150 gm of bread (70% amaranth with 30% chickpea) will provide approximately 50% of recommended amount of iron per day. The 70% of amaranth and 30 % chick pea bread will provide 15.16 mg of iron per 100 gm bread ([11](#_ENREF_11)). So the bread will meet the daily iron requirement for amaranth70%/chickpea30% group by estimating the absorption of iron at 15% -20% ([19](#_ENREF_19)). Both maize and amaranth grain flour will be prepared and packed separately. After packing each package will be labeled with a pre-printed sticker containing the id number. Two boxes per kebelle will be packet and labeled with the respective bread distributor name. In this way we ensure that the distributor gets the right box of bread and the participant the right bread. It will further be easy to keep track of ‘unopened’/’returned’ bread packages at the coordinator level every day in case of refusals or absenteeism.

Amaranth will be soaked in water by adding 5 ml of lemon juice per 100ml of water for 24 hours and germinate for 72 hours. After sun drying it will be roasted and milled with a local electrical mill ([11](#_ENREF_11)).This will decrease the phytate level and is expected to increase iron absorption in the gut. For the maize100% group the same size of bread which is prepared from roasted maize will be provided.

Both amaranth and maize bread will be made in separate local commercial bread making factories to decrease contamination or mixing of the bread. The bread will contain 5ml oil and 5ml sugar. The target daily intake of bread will be 150g for all children, considered to be an amount that they could comfortably consume in one session. The micronutrient and energy level is specified in Table 1below.

Table 1 Nutrient Content of Formulated Bread Compare to Maize Bread

| 100g | Protein mg/100gm | Fat mg/100gm | Iron mg/100gm | Calcium  mg/100gm | Zinc mg/100g | Energy  K.cal |
| --- | --- | --- | --- | --- | --- | --- |
| 100%maize | 7.58 | 4.44 | 4.31 | 24.82 | 2.47 | 386 |
| 70%amaranth and 30% c.pea | 16.39 | 7.08 | 15.16 | 244.71 | 2.59 | 404 |

[figure not shown]

[figure not shown]

[figure not shown]

[figure not shown]

Flour

Roasted

Socked

Amaranth ingarden

Figure 2 Steps of homemade amaranth processing

# Study variables

The primary outcome measure of this study will is hemoglobin of children and serum ferritin. The secondary outcomes are anthropometry measures (height/length, weight and mid-upper-arm circumference) (anthropometric z- scores will be derived based on WHO growth standards 2006 (give reference)), conjunctiva pallor and child morbidity pattern including hospitalization, diarrhea, cough and fever (type, frequency, duration and symptoms of illnesses). Potential effect modifiers and confounders will be captured to describe the population and look at the successfulness of randomization (sex, education level, occupation and income), dietary practices (number of meals and frequency of food consumption) including use of amaranth in the diet and type of staple foods.

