**Methodology:** A cross sectional study and a randomized controlled trial will be done. For the survey, random sampling will be used to select 340 children. Hemoglobin, serum ferritin, C- reactive protein and anthropometric measurements will be taken and used as the baseline data for the experimental study. In the randomized controlled trial, 100 children with hemoglobin level of less than 11 mg /dl and above 7 mg/dl (mild and moderate anemia) will be recruited into the trial after informed consent. Severely ill individuals will be referred to Hawassa Referal Hospital. Kebele-stratified simple random sampling will ensure 1:1 allocation to each group. Sequentially numbered, opaque, sealed envelopes will be used to assure concealment of allocation. The study subjects and parents (other caregivers in the absence of parents) will be kept uniformed about the trial allocation. Statistical analysis will be done using the latest SPSS version and ENA for SMART software. The survey will present descriptive statistics including frequencies, means, ranges and demographic characteristics of the population. The trial will be analyzed according to the intention-to-treat principles using logistic crude and site adjusted regression models with a mean difference in Hemoglobin as the primary outcome measure.

**Conclusion:** This research project has the potential to be hypothesis generating and will inform policy makers and scientists about amaranth’s potential to combat malnutrition specifically iron deficiency in the area.

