## **2.1. Research questions**:

1. What is the prevalence of iron deficiency anemia defined as Hemoglobin below 11mg/dl and serum ferritin below 12µg/L among children from 24.0 to 59.9 months of age in southern Ethiopia?
2. Does consumption of 150 mg bread daily containing 70 mass percentage amaranth grain increases mean hemoglobin level by 0.7mg/dl among children 24.0-59.9 months of age compared to equivalent amount of 100 percent maize bread in southern Ethiopia?
3. Is Amaranth grain culturally acceptable and how is the policy direction towards amaranth grain to use as staple food in Ethiopia?

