## 2.2. Hypothesis of this study

**HO:** Feeding 150gm of bread containing 70 mass percentage amaranth grain and 30 mass percentage chickpea per day for mild and moderate anemic children 24.0 up to 59.9 months of age for 6 months will not increase the mean hemoglobin level by 0.7g/dl compared to 150gm of 100 percent Maize containing bread in Tulla sub city southern Ethiopia.

**HA**: Feeding 150gm of bread containing 70 mass percentage amaranth grain and 30 mass percentage chickpea per day for mild and moderate anemic children 24.0 up to 59.9 months of age for 6 month will increase the mean hemoglobin level by 0.7g/dl compared to 150gm of 100 percent maize bread in Tula sub city ,southern Ethiopia.

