## Sample Size

The base line data (survey part) will be used as a basis for the trial part. After completing the survey part the trial sample will be recruited from the survey study participants, in this way the survey will be providing the baseline data for the trial. The survey sample size will be 340 considering a need for 100 trial participants, 33% of mild and moderate anemia prevalence in south Ethiopia, 0.5 degree of precision and 95% confidence intervals. The survey sample size may be increased till the numbers of eligible individuals are identified for the trial if anemia is less prevalent than 33%.

The sample size of the trial is calculated by using Stata I.C. 14 software using the sample size command, considering 0.7 mean difference,1 standard deviation, power 90% and attrition rate 12% the total sample size will be 99 (100) in the two groups. The total sample will be divided in to the amarnth70%/chickpea30% versus the maize 100% groups. Thus it will be 50 in the amaranth/chickpea group and 50 in the maize group ([2](#_ENREF_2)).

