# Statistical methods

Data will be entered in to epidata.dk and transferred in to SPSS (version 20.0) software for analysis. ENA for SMART software will be used to convert anthropometric data (weight, height) to z-scores and percent of the median in terms of wasting, underweight and stunting. Data on hemoglobin and serum ferritin levels will be described by using descriptive statistics (mean and percentages) and will be summarized by using tables and figures.

Data on dietary practices, nutritional status, morbidity patterns and serum levels will be described by using descriptive statistics (mean and percentages) and will be summarized by using tables and figures. The descriptive variables will be presented by arm to assess successfulness of the randomization and to describe the study population. Intention to treat analysis using logistic analysis for the main trial outcome hemoglobin will be done and adjustment will only be done for skewed and potentially confounding factors.

Further, descriptive statistics including morbidity prevalence and dietary practices and food diversity will be described from the survey. The relationships between variables such as sex and type of illness which are categorical in nature will be established by using chi-square. Paired t - test will be used to determine if there is a significant difference between the dietary practices (number of meals, diet diversity score), nutritional status, morbidity patterns (frequency and duration of illness), mean hemoglobin level and serum ferritin levels. Simple regression analysis will be used to determine the contribution of dietary practices and morbidity patterns to nutritional status hemoglobin and serum ferretin levels. Multiple regression analysis will be used to determine the extent to which dietary practices and morbidity patterns predict hemoglobin serum ferritin and nutritional status.

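### Study variables makes serum ferritin primary alongside hemoglobin, while the Summary, the hypothesis, the sample size and Statistical methods rest on hemoglobin alone

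*Protocol*

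**What the plan says.** Study variables reads "The primary outcome measure of this study will is hemoglobin of children and serum ferritin". It then gives anthropometry, conjunctival pallor and morbidity as secondary outcomes, so ferritin is placed in the primary tier and not merely mentioned.

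The other places point to hemoglobin alone:

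- The Summary (Methodology) describes the trial analysis "with a mean difference in Hemoglobin as the primary outcome measure".
- Statistical methods says "Intention to treat analysis using logistic analysis for the main trial outcome hemoglobin will be done".
- The alternative hypothesis (2.2) is that the amaranth and chickpea bread "will increase the mean hemoglobin level by 0.7g/dl compared to 150gm of 100 percent maize bread". Research question 2 and general objective two are also framed on hemoglobin only.
- Sample Size has one set of inputs, "considering 0.7 mean difference,1 standard deviation, power 90% and attrition rate 12" percent, and concludes "Thus it will be 50 in the amaranth/chickpea group and 50 in the maize group". The 0.7 is the hemoglobin difference of the hypothesis. Nothing is given for ferritin.

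Ferritin appears elsewhere as a separate specific objective under general objective two, and in the PICO outcome list without a rank.

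**The concern.** A protocol has to fix which result decides the trial. An analysis plan may add detail to the primary outcome, but it should not have to choose between two versions of it. Read by Study variables, a difference in ferritin alone could be reported as a result on a primary outcome. Read by the Summary or Statistical methods, the same result would be secondary. Unless this is settled before the data are seen, the label attached to a ferritin result is open to argument.

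Taking Study variables at its word also breaks the link with the sample size, which was worked out for one outcome. Two primary outcomes need either a way to share the error rate or enough power for both to succeed, and the stated inputs provide for neither.

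**Working it through.** **1. Does the stated sample size belong to one endpoint?**

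Inputs from Sample Size: difference 0.7, standard deviation 1, power 90%, attrition 12%, two equal groups. The trial's significance level is not stated; two-sided 5% is assumed here.

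- Normal approximation: n per arm = 2 × (1.960 + 1.282)² × 1² / 0.7² = 2 × 10.51 / 0.49 = 42.9, so 43 per arm and 86 in total. With attrition: 86 / 0.88 = 97.7, so 98.
- t-test version: 44 per arm, 88 in total. With attrition: 88 × 1.12 = 98.6, so 99; or 88 / 0.88 = 100.

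The stated 99 (100) is reproduced. One-sided 5% gives 36 per arm by the t-test, 72 in total, and 72 × 1.12 = 80.6 or 72 / 0.88 = 81.8, which does not match. The figure is therefore consistent with one endpoint tested at the full two-sided 5%, with nothing set aside for a second.

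**2. What if Study variables were followed and either outcome sufficed?**

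The protocol does not state this rule. With each outcome tested at an assumed two-sided 5%:

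- Independent tests: 1 − (1 − 0.05)² = 1 − 0.9025 = 0.0975.
- Correlated tests: 1 − P(|Z₁| < 1.96 and |Z₂| < 1.96) under a bivariate normal distribution.

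| Assumed correlation of the test statistics | Chance of at least one false positive | Ratio to 5% |
| --- | --- | --- |
| 0 | 9.75% | 1.95 |
| 0.5 | 9.07% | 1.81 |
| 0.7 | 8.35% | 1.67 |
| 0.9 | 7.04% | 1.41 |

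The document gives no correlation between hemoglobin and ferritin, so the table is a range and not an estimate.

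**3. What if both were required?**

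The false-positive rate would not exceed 5%. Joint power = P(hemoglobin succeeds) × P(ferritin succeeds, given that hemoglobin does). The first factor is about 0.90 with 44 evaluable children per arm. The second is below 1 unless ferritin is certain to succeed whenever hemoglobin does. Joint power is therefore below the planned 90%. The shortfall cannot be computed, because the protocol gives no effect size or standard deviation for ferritin.

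**4. When are the two outcomes measured?**

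- Table 4 marks hemoglobin at month 2 (the survey, which supplies the baseline) and at months 4, 5, 7 and 8, and ferritin at months 2 and 8.
- Figure 3 has hemoglobin every 3 months, and ferritin at the beginning and end, given as months 1 and 6.
- The section on individual advantage and disadvantage has both hemoglobin and ferritin tested at mid-study, and blood drawn three times.

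These accounts do not agree on the number of hemoglobin measurements or on whether ferritin has a mid-study value. The hypothesis refers to 6 months of feeding, which points to the end of feeding, but no section names the deciding visit.

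**The case against.** The strongest reply is that the intention is plain. The Summary, research question 2, the hypothesis, general objective two, the sample size and Statistical methods all rest on hemoglobin, and one sentence departs from them. This stands: the defect is an inconsistency to reconcile, not evidence that the trial was designed around two endpoints. It does not remove the defect, because the sentence that departs sits in the section that defines the outcomes.

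A reader might also infer stronger things, which the documents do not support:

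- *The trial carries nearly twice the nominal false-positive risk.* No rule that either outcome suffices is stated, and the 5% level and the correlations are assumptions. The absence of a multiplicity rule is not itself a fault, since such a rule may sit in a statistical analysis plan that is not shown.
- *Joint power is 81%.* That is 0.9 × 0.9 and needs independence and 90% power for ferritin. Nothing in the protocol supports either.
- *Any of four hemoglobin visits could be declared primary, giving 13% to 16%.* Nobody proposes such a rule, the hypothesis points to the end of feeding, and the count of four conflicts with the other accounts of measurement times.
- *Ferritin is analysed without regard to inflammation.* The protocol schedules C-reactive protein with ferritin and is silent on its use; it does not state an unadjusted analysis. The ferritin model may properly be left to the analysis plan. Adjusting for C-reactive protein measured after randomization could condition on something the intervention affects. The definition "Hemoglobin below 11mg/dl and serum ferritin below 12µg/L" belongs to the survey's prevalence question, a separate objective.

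**Conclusion.** The point holds as a contradiction within the protocol. Study variables has two primary outcomes; the Summary and Statistical methods have one, and the hypothesis, general objective two and the sample size are built on that one. This conclusion needs no assumption.

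The numerical consequence is conditional on which reading is adopted. Success on either outcome would mean a false-positive risk of 9.75% under independence, or about 8.3% to 9.1% at correlations of 0.7 to 0.5, taking 5% per test. Requiring both would leave that risk uninflated and lower power by an unknown amount. Neither reading of the two-outcome sentence matches the calculation behind 99 (100), whereas hemoglobin as sole primary outcome does.

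**What to change.** In Study variables, name hemoglobin at the end of the 6-month feeding period as the single primary outcome, and list serum ferritin and the earlier hemoglobin measurements as secondary. Reconcile the hemoglobin and ferritin measurement times in Table 4, Figure 3 and the section on individual advantage and disadvantage, so that the primary measurement can be identified without doubt. Make the change before any comparison between arms is seen.

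The cost is wording, and that ferritin loses primary status. The sample size stays at 99 (100), and no child or sample is added on account of the primary outcome.

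Keeping ferritin as a second primary outcome would cost more. Under an equal split of 2.5% each, hemoglobin power with 44 evaluable per arm falls from about 90% to about 84–85%. Restoring 90% for hemoglobin alone needs 51 to 52 evaluable per arm, that is 102 / 0.88 = 115.9 to 104 / 0.88 = 118.2, or 116 to 119 children in total. Ferritin would still need its own effect size and standard deviation.

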# Statistical methods

Data will be entered in to epidata.dk and transferred in to SPSS (version 20.0) software for analysis. ENA for SMART software will be used to convert anthropometric data (weight, height) to z-scores and percent of the median in terms of wasting, underweight and stunting. Data on hemoglobin and serum ferritin levels will be described by using descriptive statistics (mean and percentages) and will be summarized by using tables and figures.

Data on dietary practices, nutritional status, morbidity patterns and serum levels will be described by using descriptive statistics (mean and percentages) and will be summarized by using tables and figures. The descriptive variables will be presented by arm to assess successfulness of the randomization and to describe the study population. Intention to treat analysis using logistic analysis for the main trial outcome hemoglobin will be done and adjustment will only be done for skewed and potentially confounding factors.

Further, descriptive statistics including morbidity prevalence and dietary practices and food diversity will be described from the survey. The relationships between variables such as sex and type of illness which are categorical in nature will be established by using chi-square. Paired t - test will be used to determine if there is a significant difference between the dietary practices (number of meals, diet diversity score), nutritional status, morbidity patterns (frequency and duration of illness), mean hemoglobin level and serum ferritin levels. Simple regression analysis will be used to determine the contribution of dietary practices and morbidity patterns to nutritional status hemoglobin and serum ferretin levels. Multiple regression analysis will be used to determine the extent to which dietary practices and morbidity patterns predict hemoglobin serum ferritin and nutritional status.

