# PICO

P- Children aged 24.0 -59.9 months in southern Ethiopia, Tulla sub city, with mild and moderate anemia

I - Daily feeding of 150g bread containing 70 mass % amaranth grain and 30 mass % mashed chickpea

C -Daily feeding of 150g bread containing 100% maize

O- Change in hemoglobin level, change in ferritin status, changes in anthropometric status.

The research questions will be answered in three subsequent papers and the general and specific objectives are given below for the three papers.

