**Specific objective**

1. To compare the hemoglobin values in children receiving amaranth grain containing bread and children receiving maize bread in Tulla sub city South Ethiopia.
2. To compare the ferritin values in children receiving amaranth grain containing bread with children receiving maize bread in Tulla sub city south Ethiopia.
3. To compare the anthropometry indices in children receiving amaranth grain containing bread with children receiving maize bread in Tulla sub city south Ethiopia.
4. To compare incidence of childhood illness in children receiving amaranth grain containing bread with children maize bread in Tulla sub city south Ethiopia.
5. To compare cost effectiveness of amaranth containing bread on the prevention of iron deficiency anemia in Tulla sub city south Ethiopia
6. To compare compliance and adherence of mother between amaranth containing bread and maize bread groups.

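### Objective 3 asks for a between-arm comparison of anthropometry, but the tests named for nutritional status are a paired t-test and regressions without arm, and neither can give that comparison

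*Protocol*

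**What the plan says.** **The objective.** Under General objective two, specific objective 3 reads: "To compare the anthropometry indices in children receiving amaranth grain containing bread with children receiving maize bread". Study variables makes anthropometry secondary: "The secondary outcomes are anthropometry measures (height/length, weight and mid-upper-arm circumference", with z-scores from the WHO 2006 standards. The PICO section frames the outcomes as change: "Change in hemoglobin level, change in ferritin status, changes in anthropometric status".

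**The methods.** The Statistical methods section does the following with anthropometry or nutritional status:

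- Processing: "convert anthropometric data (weight, height) to z-scores and percent of the median in terms of wasting, underweight and stunting".
- Description: "Data on dietary practices, nutritional status, morbidity patterns and serum levels will be described by using descriptive statistics (mean and percentages".
- Presentation by arm, with its purpose stated: "The descriptive variables will be presented by arm to assess successfulness of the randomization and to describe the study population".
- A paired test: "Paired t - test will be used to determine if there is a significant difference between the dietary practices". The list that follows in that sentence includes nutritional status, hemoglobin and ferritin.
- Simple and multiple regressions with nutritional status among the outcomes, and dietary practices and morbidity patterns as the predictors.

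The intention-to-treat analysis named in that section is for one outcome: "Intention to treat analysis using logistic analysis for the main trial outcome hemoglobin will be done".

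**The concern.** The objective concerns the difference between two independent groups of children, and none of the methods attached to nutritional status estimates it. A paired t-test asks whether the same children changed between two occasions. Run within each arm, it yields two before-after results. Children aged two to five grow over six months, and both arms receive a daily bread, so a before-after change cannot be credited to either bread. A significant change in one arm and a non-significant one in the other is not evidence that the arms differ. The regressions answer another question, namely how diet and illness relate to nutritional status, because arm is not among their predictors.

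At stake is whether the trial reports an effect of the bread on growth, with its uncertainty, or a set of within-arm p-values that may be read as one.

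**Working it through.** **1. Named methods against the objective**

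| Method in Statistical methods | What it estimates for anthropometry | Arm difference? |
| --- | --- | --- |
| Conversion to z-scores and percent of the median | Nothing; data processing | No |
| Means and percentages by arm | Description and a check on randomization | No |
| Intention-to-treat analysis | Named for hemoglobin | Not named for anthropometry |
| Paired t-test | Within-child change | No |
| Simple and multiple regression | Association with diet and morbidity | No; arm not a predictor |

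**2. Data available for an arm comparison.** Sample Size says that the survey provides the trial's baseline. Table 4 schedules anthropometry at Months 2, 5 and 8, with randomization and the start of feeding in Month 3. Sampling Technique stratifies randomization by kebele. A baseline value, an end value, the arm and the stratum are therefore already planned for each child.

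**3. The plan's own sample size.** Inputs from Sample Size: difference 0.7, SD 1, power 90%, attrition 12%. Alpha is not stated for the trial; two-sided 5% is assumed. A two-sample t-test needs 44 per arm (power 0.901; 43 per arm gives 0.894), so 88 in total. 88 × 1.12 = 98.56, which rounds up to the stated 99; 88 / 0.88 = 100. The figure reproduces. It is based on the hemoglobin difference, and the protocol gives no corresponding calculation for anthropometry.

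**4. Detectable difference for anthropometry.** Assumptions not in the protocol: two-sided 5%, 80% power, equal SD at both visits, and a baseline-to-Month-8 correlation r of 0.5 to 0.9. Analysed children per arm: 50 × (1 − 0.12) = 44.

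- Month 8 values alone: the two-sample t-test with 44 per arm gives 0.604 SD.
- Regression on arm and baseline: 0.604 × √(1 − r²).
- Between-arm comparison of change from baseline: 0.604 × √(2(1 − r)).

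| r | Month 8 alone | Baseline-adjusted | Change score |
| --- | --- | --- | --- |
| 0.5 | 0.60 | 0.604 × 0.866 = 0.52 | 0.604 × 1.000 = 0.60 |
| 0.7 | 0.60 | 0.604 × 0.714 = 0.43 | 0.604 × 0.775 = 0.47 |
| 0.8 | 0.60 | 0.604 × 0.600 = 0.36 | 0.604 × 0.632 = 0.38 |
| 0.9 | 0.60 | 0.604 × 0.436 = 0.26 | 0.604 × 0.447 = 0.27 |

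Adjustment helps considerably against Month 8 values alone when r is high. Against a change score it saves 0.04, 0.02 and 0.01 SD at r = 0.7, 0.8 and 0.9.

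**The case against.** The strongest reply is that anthropometry is secondary, and the model for a secondary outcome is commonly left to a SAP, which is not shown here. The Summary also states, for the trial as a whole, that analysis follows intention to treat with crude and site-adjusted regression. The paragraph holding the paired t-test opens with the survey, so that test and the regressions may be meant for the survey. The paired-test sentence also covers hemoglobin and ferritin, so the fault is not peculiar to anthropometry.

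Part of this stands. If the paragraph concerns only the survey, the protocol is merely silent on the secondary trial outcomes. The text does not say so, however. A single cross-sectional survey offers no obvious pairs for a paired test, whereas the trial has repeated visits. As it reads, the protocol assigns nutritional status to tests that do not fit objective 3, which is more than leaving detail for later. The Summary's regression sentence names hemoglobin as its outcome and describes the models as logistic, so it does not supply a model for continuous z-scores.

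Three stronger readings are tempting and are not supported:

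- *That the plan reduces anthropometry to categories only.* It keeps continuous z-scores and allows means. Wasting, underweight and stunting may simply name the three indices.
- *That power is lost by comparing percentages wasted or stunted.* No cut-off and no categorical test between arms is prescribed for these outcomes, so power figures for such a test would concern an analysis that is not in the plan.
- *That most of the power is lost by ignoring baseline.* PICO frames the outcome as change, which uses the child's own baseline and, if compared between arms, recovers most of the gain at r of 0.7 or more. A large loss appears only against Month 8 values alone and under high assumed correlations.

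**Conclusion.** The point holds as a mismatch between a stated objective and the methods named for it. Objective 3 calls for an arm comparison; the paired t-test and the regressions without arm cannot provide one, and the named intention-to-treat analysis is for hemoglobin. This conclusion rests on the wording alone and needs no assumption about effect size.

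The statistical gain from the proposed model is conditional. With 44 per arm, two-sided 5% and 80% power, the detectable difference falls from about 0.60 SD to between 0.52 and 0.26 SD for r from 0.5 to 0.9, relative to Month 8 values alone. Relative to change scores it is small from r = 0.7 upward. The protocol gives no anthropometric SD, effect size or correlation, so nothing can be said about whether a real growth effect would be missed. A reader might also infer that percent of the median must be removed; that is a matter of preference and no part of this point. For a secondary outcome, this is a correction worth making rather than a threat to the trial's main result.

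**What to change.** Add to Statistical methods: *Height-for-age, weight-for-height and weight-for-age z-scores and MUAC at Month 8 will each be compared between the arms as randomised, by linear regression on arm, the same child's Month 2 value and kebele, reporting the mean difference with 95% confidence interval. Percentages wasted, underweight and stunted will be given by arm as description.*

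In the same section, state whether the paired t-test and the diet and morbidity regressions belong to the survey or the trial. If they belong to the trial, say that they are not the analysis for objective 3.

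The cost is wording only. All the measurements are already scheduled, and no additional child, visit or sample is needed.

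### Serum ferritin is summarised by means, with only a paired t-test and diet or morbidity regressions named; a baseline-adjusted log-scale comparison between arms would be more efficient if ferritin is right-skewed

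*Protocol*

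**What the plan says.** Statistical methods gives ferritin the same descriptive treatment as hemoglobin: "Data on hemoglobin and serum ferritin levels will be described by using descriptive statistics (mean and percentages"). Later in that section a paired t-test is listed for several variables, ending with "mean hemoglobin level and serum ferritin levels. Simple regression analysis will be used". The simple and multiple regressions that follow have dietary practices and morbidity as predictors; trial arm is not among them. The intention-to-treat analysis is stated for hemoglobin only. The section mentions no logarithm, geometric mean or rank method. Its one reference to skewness concerns which factors to adjust for, not how an outcome is distributed.

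Ferritin's standing in the trial comes from three places:
- Study variables: "The primary outcome measure of this study will is hemoglobin of children and serum ferritin".
- General objective two, specific objective 2: "To compare the ferritin values in children receiving amaranth grain containing bread with children receiving maize bread".
- The Summary, by contrast, describes the trial analysis "with a mean difference in Hemoglobin as the primary outcome measure" and does not mention ferritin there.

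In Table 4 (Trial Schedule) ferritin is measured at Month 2, before randomization in Month 3, and at Month 8. Under General objective one, the survey description of ferritin includes the median and range as well as the mean.

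**The concern.** Ferritin cannot fall below zero, and the protocol's own deficiency cut-off is 12 µg/L. Entry to the trial depends on hemoglobin, not ferritin, so depleted and replete children will be in the same sample. CRP is measured alongside ferritin. A right-skewed distribution is a reasonable expectation, but it remains an assumption because the protocol gives no ferritin SD or distribution.

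If ferritin is skewed, a few high values weigh heavily on an arithmetic mean and its standard error. A comparison of untransformed levels is then more likely to miss a proportional rise in iron stores than the same comparison on the log scale. Nothing in the design offsets this, because the sample size was set for hemoglobin alone. The plan also names no between-arm model that uses the pre-randomization ferritin value, although that value will be available for each child and could sharpen the comparison.

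**Working it through.** **Inputs from the protocol (Sample Size).** "considering 0.7 mean difference,1 standard deviation, power 90% and attrition rate 12% the total sample size will be 99 (100) in the two groups"; "Thus it will be 50 in the amaranth/chickpea group and 50 in the maize group". These figures are for hemoglobin. Alpha is not stated for the trial; the only nearby figure is for the survey ("0.5 degree of precision and 95% confidence intervals"). Two-sided 5% is assumed.

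**Reproducing the plan's figure.** With standardised difference 0.7/1 = 0.7, the t-based calculation gives 44 per arm (power 0.901), 88 in total. Then 88 × 1.12 = 98.6, so 99; 88/0.88 = 100. The stated 99 (100) reproduces. It also fixes the evaluable number used below: 100 less 12% is 88, or 44 per arm.

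**Inputs that had to be assumed.** Log-normal ferritin, the same log-SD s in both arms, and s from 0.4 to 1.2.

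**Raw against log scale, between arms.** For a two-sample t-test with 44 per arm (86 degrees of freedom), 80% power needs a standardised difference of 0.604. On the log scale the effect is therefore 0.604 × s, and the geometric mean ratio is exp(0.604 × s). For s = 0.8 that is exp(0.483) = 1.62. Log-normal data were simulated at each s (100,000 trials) and tested both on the logs and untransformed:

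| Log-SD | Ratio | Power, log | Power, raw | Loss (points) |
|---|---|---|---|---|
| 0.4 | 1.27 | 79.9% | 76.8% | 3.1 |
| 0.5 | 1.35 | 79.8% | 75.1% | 4.7 |
| 0.6 | 1.44 | 80.2% | 73.3% | 6.9 |
| 0.8 | 1.62 | 79.9% | 67.7% | 12.2 |
| 1.0 | 1.83 | 80.2% | 61.5% | 18.7 |
| 1.2 | 2.06 | 80.1% | 54.5% | 25.6 |

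A separate run of 30,000 trials per setting gave losses of 2.9, 4.9, 6.4, 12.6, 18.2 and 25.4 points, so the rounded figures are stable to about one point.

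**Fixed effect instead of fixed power.** The loss also depends on the effect. With 44 per arm and log-SD 0.5 to 1.0 it is about 5 to 7 points for a ratio of 1.3, 2 to 14 for 1.5, and 0.1 to 19 for 1.75.

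**Type I error.** With no effect, the raw-scale test rejected in 3.9% to 4.9% of trials across these log-SDs. It is not inflated.

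**If the named paired test were used as it stands.** For 44 children, an assumed baseline-to-end correlation of 0.5 and an effect giving about 78% power on the log scale, raw-scale power for change over time was 67.8%, 60.3% and 53.1% at log-SD 0.6, 0.8 and 1.0. The scale therefore matters for that test too, although it does not compare the arms.

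**Adding baseline.** Adjusting for baseline log ferritin with correlation r multiplies the residual SD by √(1 − r²). At an assumed r = 0.5 this is √0.75 = 0.866. The standardised difference rises to 0.604/0.866 = 0.698, and power goes from 80% to about 90%.

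**The case against.** The strongest reply is that the protocol never specifies the untransformed scale. The choice to log a skewed biomarker is often left to the SAP, which is not at hand. That stands in part: a reader might infer that the protocol commits to a raw-scale analysis, but it does not say so. The section is nevertheless not silent on ferritin. It names the summary statistic, the test and the models, all applied to levels, and an analyst following it literally would not transform.

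Second, the two-sample test behind the table is not in the protocol. The named t-test is paired and the regressions have no arm term. This is correct, and it means the losses describe a natural reading of the between-arm objective rather than a stated procedure. It also shows that a between-arm model for ferritin has to be written in any case.

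Third, medians are already planned. They are, in the survey objective, and the survey supplies the trial's baseline. This answers the descriptive point at baseline, but not for the end-of-trial comparison.

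Fourth, a mean difference in µg/L is a legitimate target, and no ferritin power was claimed. Both stand. They are the reason to treat this as an improvement.

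**Conclusion.** The point holds as a gain in efficiency. Read as written, the plan would compare ferritin less efficiently than it could, and it leaves the baseline measurement unused in any between-arm model. The loss from the raw scale is about 3 points of power at log-SD 0.4, 5 at 0.5, 7 at 0.6, 12 to 13 at 0.8, 19 at 1.0 and 25 at 1.2. This rests on log-normal ferritin, equal log-SD in the arms, 44 per arm, two-sided 5% and an effect giving 80% power on the log scale. The documents give neither the SD nor the effect, so no single figure from this range should be quoted as the cost; with modest skew it is under 5 points.

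Two stronger readings are not supported. A reader might infer that the ferritin analysis is invalid, but type I error stays at or below 5%. A reader might also infer that the trial fails its stated power for a primary outcome. The sample size concerns hemoglobin only, and the protocol is inconsistent on whether ferritin is primary at all (Study variables against the Summary and Statistical methods).

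**What to change.** In Statistical methods, add that the trial comparison of ferritin uses log-transformed ferritin at Month 8 in a linear model with arm, kebele (the randomization stratum) and baseline log ferritin from Month 2, reported as a ratio of geometric means with a 95% CI. In the ferritin summaries, give geometric means or median (IQR) by arm alongside the means. Keep hemoglobin on its raw scale. Fix this wording before allocation is revealed, so that the scale is not chosen after results are seen.

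The cost is wording only: no extra children, blood samples or visits. The small downside is that the effect is a ratio rather than a difference in µg/L; the difference can be shown as a supplementary summary.
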